**FIGURE 1 F1:**
[figure not shown]
Proposed study design.

In a period of 6 months, we expect that a team of trained interviewers will contact all potential cohort participants. Based on information from a recent study on the association of IC with the outcome incidence rates of functional dependence, falls, and death (Prince et al., 2021), we developed sample size estimates for comparing two proportions that represent the rates of outcomes in the groups that are exposed (low IC) and unexposed (medium or high IC) (see Tables 1, 2). Calculations considered various effect sizes (relative risk) and incidence or mortality rates. In estimating the sample size needed for this cohort study, this study considered the incidence of the expected outcome in the unexposed cohort (high IC), the risk assumed in the exposed group relative to the risk of the unexposed group (RR), a specific level of confidence (1-α = 0.95; where α = type I error rate), and a specific value of the desired sample power (1-β = 0.80; where β = type II error rate) for the detection of significant differences between the two cohorts. The outcome incidence rate in the cohort was used as a proxy for the expected outcome incidence rate in the unexposed group (high IC). The summary tables (Tables 1, 2 below) provide sample sizes for extremes of the assumed incidence and mortality rate values and the respective relative risks based on the confidence intervals of these measures. A total sample size of approximately 5,500 individuals (assuming 2,750 per group) will be sufficiently robust to maintain the desired power under most diverse scenarios and varying parameters, even if the dropout rate reaches approximately equal to 15% in the two cohorts. The exception will be with very small estimates of the relative risk of death (RR ≤ 1.3).

**TABLE 1 T1:** Sample sizes for specific values of functional loss (FL), incidence, and relative risk for intrinsic capacity (IC) and FL.

	Average risk ratio	Low risk ratio	High risk ratio
Risk ratios (RR)	1.91	1.7	3.0
Incidence rate among the unexposed group	0.0495	0.04925	0.04925
Confidence level (1-α)	0.95	0.95	0.95
Power (1-β)	0.8	0.8	0.8
Study type	Cohort	Cohort	Cohort
Sample per group (n_i_)	514	816	138
Total sample (n_1_+n_2_)	1,028	1,632	276

**TABLE 2 T2:** Sample sizes for specific values of total mortality (TM) and relative risk for IC and TM.

	Average risk ratio	Low risk ratio	High risk ratio
Risk ratios (RR)	1.66	1.3	2.0
Mortality rate among unexposed	0.04826	0.04826	0.04826
Confidence level (1-α)	0.95	0.95	0.95
Power (1-β)	0.8	0.8	0.8
Study type	Cohort	Cohort	Cohort
Sample per group (n_i_)	926	3,922	432
Total sample (n_1_+n_2_)	1,852	7,844	864

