### Explanatory variables: IC composite index (ICI)

An IC composite score or index (IC index or ICI) will first be created, as suggested by Gutiérrez-Robledo et al. (2019). This score aims to express a summary measure of impairments for an older adult. Initially, each continuous or ordinal subdomain measure will be dichotomized based on acceptable cut-off points to create a binary variable of 0 or 1 (see Table 3 for cutoff points across all subdomain measures). Within a domain, the values of these recoded subdomain measures will be summed up to create a “subdomain score.” The subdomain scores will range from 0 to 2 for the four subdomains with only two measures and from 0 to 6 for the subdomain with six measures (i.e., vitality). Then, each domain of the five IC components will be subdivided into three categories based on the sum of the scores of its subdomains, with the following numerical score: no impairment = 0, mild impairment = 1, and severe impairment = 2. For example, the four domains with only two subdomain measures (e.g., cognitive with subdomain measures memory and cognitive) will be coded 0 if their subdomain score (sum of their subdomain measure) is 0, 1 if the subdomain score value is 1, and 2 if the subdomain score value is 2. The domain with six subdomain measures, vitality (subdomains comorbidity, medication, biomarkers, pain, strength, and nutrition), will be coded 0 if its subdomain score is 0, 1 if the subdomain score is 2–4, and 2 if the subdomain score is 5–6. Scores for each of the five domains will be summed up to produce a composite IC index ranging from 0 (best possible ICI) to 14 (worst possible ICI).

Subsequently, this baseline ICI will be classified in four ways. First, using the terciles of ICI (TIC), ICI values less than or equal to the first tercile (Q1) will be classified as low TIC; ICI values between Q1 and the third tercile (Q3), including Q3, will be classified as medium TIC; and ICI values above Q3 will be classified as high TIC. This analysis model is explicitly shown in Figure 1.

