#### Statistical models to assess whether IC is a predictor of ADLs/IADLs, falls, and death

Two Cox regression models will be evaluated to estimate the incidence rates of outcomes (i.e., functional loss measured by IADLs, falls, and death) associated with IC at baseline (e.g., TIC, DIC, and WIC) (ElHafeez et al., 2021). Cox’s first model has the indicator variable X to denote the association with each of the two groups of IC exposure at baseline (e.g., X1 = 1 for medium and high TIC and X1 = 0 for low TIC), with Y being the adverse incident at 3 years of follow-up (loss of ADLs/IADLs, falls, and death); survival times will be measured by the interval from the first assessment to the adverse incident. For subjects who do not experience an adverse incident, the follow-up time will be the last evaluation of the study.

The model also comprises a collection of covariates V with the potential to be a confounding factor in the association between Y and X (e.g., sociodemographic factors), and W would be the potentially interactive term between X and V (e.g., sex * TIC). The regression coefficient of X describes the effect of TIC on outcome Y, that is, the risk of greater or lesser loss of ADL/IADL, falls, and death for those exposed to medium or high TIC relative to those exposed to low TIC. The W terms will assess whether there is a positive interaction between TIC and one of the V confounders that have been identified to be potentially interacting. The model will extend by substituting TIC for DIC or WIC as the main exposure variable X. Alternatively, we can also model Y (e.g., IADL) as a function of X (either TIC, DIC, or WIC) and the same set of V and W using logistic regression to estimate the odds ratio of the outcomes.

We will evaluate the IC trajectory through changes in IC scores (∆IC or WIC) or the presence of IC decline (DIC) after 3 years, along with their associations with IADL outcomes, falls, and death. For example, the mean/median of ∆IC (or WIC) and the prevalence of DIC will be generated at baseline and at the end of the 3-year follow-up. We will then generate the mean/median or prevalence of IC measure by levels of ADL/IADL, falls, and death. The means/medians of IADLs and the incidence of falls and death after 3 years of follow-up will also be estimated.

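### The low-IC comparator is named two ways, the upper tercile cut is misdefined, and neither tercile contrast gives the assumed 2,750 per group

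*Protocol article*

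**What the plan says.** Four places in the protocol article bear on this.

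- **Study sample size and power calculation, groups compared.** The two proportions are for "the groups that are exposed (low IC) and unexposed (medium or high IC".
- **Same paragraph, inputs.** One input is "the incidence of the expected outcome in the unexposed cohort (high IC". The rate is then justified with a second mention of high IC alone: "The outcome incidence rate in the cohort was used as a proxy for the expected outcome incidence rate in the unexposed group (high IC". The total is 5,500, assumed to be 2,750 per group.
- **Explanatory variables: IC composite index (ICI).** The lower cut is "ICI values less than or equal to the first tercile (Q1) will be classified as low TIC". The upper cut is "ICI values between Q1 and the third tercile (Q3), including Q3, will be classified as medium TIC", and then "ICI values above Q3 will be classified as high TIC". The index itself runs from 0 (best) to 14 (worst).
- **Statistical models to assess whether IC is a predictor of ADLs/IADLs, falls, and death.** The first Cox model has a two-group exposure, for example "X1 = 1 for medium and high TIC and X1 = 0 for low TIC". Its coefficient is described as the risk "for those exposed to medium or high TIC relative to those exposed to low TIC".

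**The concern.** Medium-or-high and high alone are different comparators unless medium and high IC carry the same risk. An index meant to describe graded trajectories presumes that they do not. A reader cannot tell whether an RR of 1.91 or 1.66 is the quantity that the Cox model will estimate or a ratio between the two end groups.

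The three-level classification is then reduced to two levels in the TIC model, so that model cannot show a gradient across the three groups. The upper cut does not define thirds on any reading, so any table or model that uses the high group separately has no workable rule. The planned allocation of 2,750 v 2,750 cannot arise from terciles.

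**Working it through.** **1. The plan's own figures.** Inputs are from Tables 1 and 2: two-sided alpha 0.05 (sidedness is not stated, but two-sided matches the tables), power 0.80, equal groups. With p1 = RR × p0,

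n = (1.960 + 0.842)² × [p0(1 − p0) + p1(1 − p1)] / (p1 − p0)².

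| Outcome | RR | p0 | Table n | Recomputed n |
|---|---|---|---|---|
| Functional loss | 1.91 | 0.0495 | 514 | 514 |
| Functional loss | 1.7 | 0.04925 | 816 | 816 |
| Functional loss | 3.0 | 0.04925 | 138 | 140 |
| Death | 1.66 | 0.04826 | 926 | 926 |
| Death | 1.3 | 0.04826 | 3,922 | 3,922 |
| Death | 2.0 | 0.04826 | 432 | 449 |

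The tables reproduce closely apart from the last cell; both high-RR cells match exactly at a rate of 0.05. At 2,750 per group, power is at least 0.998 for every RR except 1.3 (0.65), so the plan's power statement holds on its own terms.

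**2. Group sizes.** Thirds of 5,500 are 5,500 / 3 ≈ 1,833. Low versus the rest is 1,833 v 3,667. Low versus high is 1,833 v 1,833. Neither is 2,750 v 2,750.

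**3. The upper cut.** Three groups need two cuts. A third tercile taken literally is the maximum, so nobody lies above it. If Q1 and Q3 are quartile labels, the groups are about 25%, 50% and 25%.

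**4. Effect of pooling medium with high, if the tabulated RRs are low versus high.** The risk in the medium group is not given. Assume it is m × p0 with m = √RR (geometric mean) or m = (1 + RR)/2 (midway), and that medium and high are of equal size. The pooled comparator risk is p0(1 + m)/2, so the pooled RR is RR / [(1 + m)/2].

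| RR, low v high | Geometric mean | Midway |
|---|---|---|
| 1.91 | 1.91 / 1.191 = 1.60 | 1.91 / 1.2275 = 1.56 |
| 1.66 | 1.66 / 1.144 = 1.45 | 1.66 / 1.165 = 1.42 |
| 1.3 | 1.3 / 1.070 = 1.21 | 1.3 / 1.075 = 1.21 |

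If m = 1, or if the RRs already compare low with the rest, there is no attenuation.

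**5. Power for that case.** Assume 1,445 per third (6,000 × 0.85 × 0.85 / 3: 15% refusal, then 15% loss). Power = Φ(|difference| / SE − 1.96), unpooled variance. For death, RR 1.66, medium midway:

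- Low: 0.04826 × 1.66 = 0.0801. Pooled comparator: 0.04826 × 1.165 = 0.0562.
- SE = √(0.0801 × 0.9199 / 1,445 + 0.0562 × 0.9438 / 2,890) = 0.00833.
- Power = Φ(0.0239 / 0.00833 − 1.96) = Φ(0.91) ≈ 82%.

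The geometric-mean case gives 85%. Low versus high directly (1,445 v 1,445) gives 94%. If medium and high risks are equal, the pooled contrast gives 97% against 94% for the direct one.

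Starting instead from 5,500 with 15% loss (1,558 per third), medium midway and a pooled-variance formula, power is 0.98, 0.905 and 0.87 for RR 1.91, 1.7 and 1.66, and 0.34 for 1.3. Only when medium risk comes close to low-IC risk does power fall below 80% for the first three. At exact equality it is 0.76, 0.57 and 0.52.

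**6. Direction of the index.** Because 0 is best, ICI at or below the first cut is the best-capacity group. On that literal reading, X1 = 1 pools medium with worst and compares them with best. The RR becomes (m + RR)/2. For 1.91 that is (1.382 + 1.91)/2 = 1.65, or (1.455 + 1.91)/2 = 1.68.

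**The case against.** The strongest reply is that the main comparison is consistent by label. The sample-size section first sets low against medium or high, and the Cox model uses the same grouping in both code and words. High IC alone appears only as a gloss on the unexposed group in the sample-size inputs. This stands. A reader might infer that the plan intends a low-versus-high contrast which the Cox model then dilutes or fails to estimate. The document does not support that: no analysis section plans such a contrast, and the article does not say that the RRs describe one.

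Two further points also stand. The coded contrast depends only on the lower cut, so the error in the upper cut leaves X1 unchanged. The two-group TIC coding is not the only exposure either: it is given as an example, and the weighted score WIC, which has more levels, can replace it, so a gradient is not hidden from every planned analysis.

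A reader might also infer that the study is underpowered. Under the graded assumptions it is not, because 5,500 is well above most of the tabulated requirements.

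What the reply does not remove is that one paragraph gives two comparators, that the cut rule is wrong as written, and that the group sizes fit neither contrast. The index direction adds to this: an intermediate person falls in the better-capacity or the worse-capacity group depending on whether the reader follows the label or the score.

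**Conclusion.** The point holds as a definitional fault of modest numerical size. The comparator is ambiguous, the upper cut is unusable, and the 2,750 per group does not follow from terciles. Attenuation to about 1.56-1.60 (from 1.91) or 1.42-1.45 (from 1.66) is conditional on two things that the article does not state: that the RRs are low versus high, and that medium risk lies between the two. On the literal index direction, 1.91 becomes about 1.65-1.68 instead. Power stays above 80% under these graded assumptions, except for the death RR of 1.3 that the plan already excepts.

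The calculation takes the tabulated rate as the high-IC risk, although the plan uses the whole-cohort rate as a proxy for it. It also assumes equal thirds and lets a two-proportion test stand in for the Cox model.

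**What to change.** - **Index section:** set the cuts at the first and second terciles (33.3rd and 66.7th percentiles) and label the groups by capacity (best, middle, worst), so that the direction of scoring no longer matters.
- **Sample-size section and Cox section:** name one comparator, say which contrast the RRs refer to, and restate group sizes and power for the real split.
- **Cox section:** fit TIC as a three-level factor with the best-capacity third as reference, and add a trend test. The pooled contrast may stay alongside; demoting it would be a preference, not a correction.

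The cost is wording, one extra parameter and a rerun of the power calculation. The article says that no data have been collected, so the change cannot look data-driven. The downsides are small. The worst-versus-best interval is somewhat wider if middle and best risks are in truth equal (about 94% v 97% power at RR 1.66, assuming 1,445 per third). Ties in an integer score will make the thirds only approximate.

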## Research questions and hypotheses to test

This proposed research will answer three scientific questions:1. Whether IC will decrease as expected at the 3-year follow-up (ICI at end-time ≤ ICI at baseline, or ∆IC < 0), regardless of the socioecological context, individual sociodemographic, behavioral, and clinical factors, and comorbidities (Charlson et al., 1987). This research will statistically test the hypothesis that ICI will not change over time (i.e., follow up IC = baseline IC, or ∆IC = 0).2. If DIC (or TIC) at baseline will be a strong predictor of FA, such as ADL (Mlinac and Feng, 2016), IADL (Hokoishi et al., 2001), falls (Kitcharanant et al., 2020), and death, regardless of the socioecological context, individual sociodemographic, behavioral, and clinical factors, and comorbidities (Charlson et al., 1987). That is, whether the proportion of these ADL/IADL losses, falls, and deaths will be greater in the decline group (e.g., DIC present) than in the unexposed group (e.g., DIC absent). Research will statistically test the hypothesis that there is no association between IC and ADL (or IADL) (e.g., relative risk for TIC or DIC and IADL = 1).3. Whether IC and its five domains are directly associated with a measure of QoL (i.e., World Health Organization Disability Assessment Schedule 2.0 (WHODAS 2.0)) (Prüss-Ustün et al., 2017) and LTPA (i.e., the International Physical Activity Questionnaire (IPAQ)) (Craig et al., 2003), regardless of the socioecological context, individual sociodemographic, behavioral, and clinical factors, and comorbidities (Charlson et al., 1987). Research will statistically test the hypothesis that there is no association between IC and either QoL or LTPA (e.g., relative risk for TIC or DIC and LTPA = 1).

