### Data analysis

The analysis will be implemented in SAS Institute Inc (2023). For all analyses at baseline and final follow-up time, descriptive statistics (e.g., frequency, central trend, and variability) and diagnostic plots (e.g., histogram or kernel density estimation and q–q plots) will be implemented on all variables. Data for outliers will be evaluated and tested as needed for statistical model assumptions. Appropriate corrective strategies, such as transformations, the use of robust methods, and/or data reduction, will be used if problems are identified.

These preliminary analyses aim to ensure high-quality data and test the assumptions of the proposed statistical models. We assume that this study (cohort) suffers from an uneven distribution of confounding factors, which may be exacerbated by the bias due to the possible unequal dropout rates between exposure groups. Therefore, adequate adjustment of the characteristics of the study subject is crucial to make an unbiased inference of the associations between the outcomes of interest (addiction, falls, and mortality) and the main exposure factor, IC, and the associations between IC and its five domains (vitality, mobility, sensory, cognitive, and psychological) and the evolution of IC in the follow-up time.

It is also expected that not all values for all variables will be collected, thus generating observations with missing values. If there is a substantial number of unused cases under analysis due to missing values (≥5%), multiple imputations of these values will be used along with a corresponding sensitivity analysis. In the sensitivity analysis, models with the inclusion of imputed missing data will be compared to original models in which missing data are not included. If there is a substantial change in the parameters of interest between these two models (e.g., a nonsignificant coefficient in the original model becomes significant in the model with imputed data), the imputed model will be accepted as the least-biased model in terms of the bias introduced by the missing values of variables.

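### The stated power exception (death RR of 1.3 or less) is too narrow: with the plan's own inputs 80% power starts at about RR 1.40 crude, and at about 1.42 to 1.52 in the adjusted test that answers question 2

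*Protocol article*

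**What the plan says.** In *Study sample size and power calculation*, the article reports "sample size estimates for comparing two proportions that represent the rates of outcomes in the groups" with low IC and with medium or high IC. The power of 80% is set "for the detection of significant differences between the two cohorts". Tables 1 and 2 use four inputs only: the relative risk, the rate in the unexposed, 95% confidence and 80% power. They give sizes per group of 514, 816 and 138 for functional loss (RR 1.91, 1.7, 3.0) and 926, 3,922 and 432 for death (RR 1.66, 1.3, 2.0). The text then attaches the power claim to a total of about 5,500, taken as 2,750 per group. It describes this as adequate in most scenarios with dropout near 15%, and names a death RR of 1.3 or less as the exception.

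The analysis is of another kind. In *Research questions and hypotheses to test*, question 2 asks whether IC predicts functional outcomes, falls and death "regardless of the socioecological context, individual sociodemographic, behavioral, and clinical factors, and comorbidities". *Data analysis* assumes that confounders are unevenly distributed and says that "adequate adjustment of the characteristics of the study subject is crucial to make an unbiased inference". The section on models for ADLs/IADLs, falls and death specifies Cox regression, or alternatively logistic regression, with a set of covariates V alongside the IC term.

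**The concern.** The sizing describes a test without covariates, while the test that answers question 2 has them. When covariates explain a share R² of the variation in IC group, the variance of the IC coefficient rises by roughly 1/(1 − R²), and the size needed for a given power rises by the same factor. The plan's premise of uneven confounders means that R² is above zero. There is also a structural reason: question 2 adjusts for comorbidities and clinical factors, and Table 3 builds the vitality domain partly from the number of chronic morbidities and medications.

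What is at stake is the detection limit. A reader of the exception will take it that death RRs a little above 1.3 are covered. If the adjusted analysis then gives a non-significant result for a true RR of 1.4, that reader would wrongly treat it as informative.

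**Working it through.** **Inputs.** From the article: mortality in the unexposed p0 = 0.04826; α = 0.05 (two-sided, which reproduces the tables); power 0.80; 5,500 participants; 1:1 split; 15% dropout. Retained: 5,500 × 0.85 = 4,675, or 2,337.5 per group. Assumed, because the document gives no value: R² between IC group and covariates of 0.1 to 0.4.

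**Step 1, reproduce the tables.** n per group = (1.960 + 0.842)² × [p0(1 − p0) + p1(1 − p1)] / (p1 − p0)², with p1 = p0 × RR and (1.960 + 0.842)² = 7.849.

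- Death RR 1.66: p1 = 0.08011; 7.849 × 0.11962 / 0.03185² gives 926 (stated 926).
- Death RR 1.3: p1 = 0.06274; 7.849 × 0.10473 / 0.01448² gives 3,922 (stated 3,922).
- Functional loss RR 1.91 and 1.7: 514 and 816 (stated 514 and 816).
- Functional loss RR 3.0 and death RR 2.0: 140 and 449 (stated 138 and 432). These two differ slightly and do not affect the point.

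The tabled sizes are therefore crude sizes with no allowance for covariates.

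**Step 2, crude detection limit at 2,337.5 per group.** Solve the same formula for RR. At RR = 1.396, p1 = 0.06737, the variance sum is 0.04593 + 0.06283 = 0.10876 and the difference is 0.01911, so n = 7.849 × 0.10876 / 0.01911², or about 2,337. The crude limit is about 1.40, not just above 1.3. Even with no dropout (2,750 per group) it is about 1.36.

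**Step 3, adjusted detection limit.** Replace 2,337.5 by 2,337.5 × (1 − R²):

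| R² (assumed) | Smallest death RR with 80% power | Power at death RR 1.4 |
|---|---|---|
| 0 | 1.40 | 81% |
| 0.1 | 1.42 | 77% |
| 0.2 | 1.45 | 72% |
| 0.3 | 1.48 | 66% |
| 0.4 | 1.52 | 59% |

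The last column is Φ(z√(1 − R²) − 1.960). Here z = (0.06756 − 0.04826) / √(0.10893/2,337.5) = 2.828. At R² = 0 this is Φ(0.868) = 81%; at R² = 0.3 it is Φ(2.366 − 1.960) = 66%.

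**Step 4, the tabled scenarios at the planned size.** At 2,337.5 per group and R² = 0.4, power is about 93% for death RR 1.66, 96% for functional loss RR 1.7, and over 99% for functional loss RR 1.91 and 3.0 and death RR 2.0. For death RR 1.66, power reaches 80% only at R² = 1 − 926/2,337.5 = 0.60. Death RR 1.3 has 58% power with no adjustment at all.

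**Step 5, unequal split.** The Cox model contrasts one tercile with the other two. With one third exposed (about 1,558 against 3,117 of 4,675) and the same unpooled variance, the limit is about 1.43 crude and 1.53 at R² = 0.3. The 1:1 figures are the favourable case.

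**The case against.** The strongest reply is that the study will not be run at the tabled sizes. The power claim is tied to about 5,500. After dropout that leaves some 2,338 per group, against a largest non-excepted requirement of 926, and this margin absorbs any R² up to about 0.6. This stands. A reader might infer that the study's power falls from 80% to 76%, 71%, 65% or 58% for R² of 0.1 to 0.4. Those figures hold only at the tabled sizes and do not describe the planned cohort.

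A second reply is that the one scenario that fails is already disclosed, and that the gap from 1.30 to 1.40 exists before any adjustment. Both statements are true. The second is itself a reason to restate the exception, and adjustment then widens the gap. The claim is also hedged to most scenarios, and no death RR between 1.3 and 1.66 is tabled. But the exception as worded still implies coverage in that interval.

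Third, R² is nowhere in the document, and 1/(1 − R²) counts only the loss of precision. In Cox or logistic models, adjusting for strong predictors of outcome can move the conditional effect away from 1 and offset part of the loss. Conversely, if the input RRs are crude, removing confounding could bring the adjusted RR closer to 1. The article does not say which they are. The adjusted figures are therefore a range, not a prediction.

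**Conclusion.** The point holds as a misstated detection limit, not as a shortage of participants. With the plan's own inputs, 80% power for death starts at an RR of about 1.40 crude and about 1.42 to 1.52 in the adjusted test for R² of 0.1 to 0.4, against a stated exception that ends at 1.3. This rests on 15% dropout, a 1:1 split, the two-sided unpooled formula that reproduces the main tabled sizes, an assumed R² range, and precision loss only.

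Two wider readings are not supported. One is that every hypothesis loses its stated power. Tables 1 and 2 cover only functional loss and death, which are part of question 2; questions 1 and 3 have no stated power to lose. The other is that recruitment must rise. All tabled scenarios other than death RR 1.3 keep over 90% power throughout the assumed range.

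**What to change.** - Replace the exception for death RR of 1.3 or less by the minimum detectable adjusted RR at 4,675 retained, over a stated range of R². For death this is about 1.4 to 1.5 with a 1:1 split.
- Label the sizes in Tables 1 and 2 as crude, or divide each by (1 − R²). For death RR 1.66, 926 per group becomes 1,029, 1,158, 1,323 and 1,544 at R² of 0.1, 0.2, 0.3 and 0.4.
- State whether the input RRs are crude or adjusted, and for what.
- Give R² as an explicit assumption. The earlier cohort in the same area should not be relied on to supply it, because the article does not say that it measured the IC components.

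The cost is a recalculation and a slightly less favourable power statement. The article says that no data have been collected, so the change can be made before enrolment, and the recruitment target need not move.

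### Tables 1 and 2 enter the whole-cohort event rate as the unexposed rate; with every relative risk above 1, all six sample sizes per group are too small for their stated 80% power

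*Protocol article*

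**What the plan says.** The Protocol article, under Study sample size and power calculation, sizes the study by comparing two proportions, exposed (low IC) against unexposed, with 95% confidence and 80% power. It lists its inputs: "this study considered the incidence of the expected outcome in the unexposed cohort (high IC), the risk assumed in the exposed group relative to the" unexposed risk. It then says where the unexposed rate came from: "The outcome incidence rate in the cohort was used as a proxy for the expected outcome incidence rate in the unexposed group (high IC").

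Table 1 (functional loss) prints "Incidence rate among the unexposed group 0.0495 0.04925 0.04925" with "Risk ratios (RR) 1.91 1.7 3.0", and gives 514, 816 and 138 per group. Table 2 (death) prints "Mortality rate among unexposed 0.04826 0.04826 0.04826" with "Risk ratios (RR) 1.66 1.3 2.0", and gives 926, 3,922 and 432 per group.

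The text concludes that about 5,500 participants, taken as 2,750 per group, hold the desired power in most scenarios even with about 15% dropout. It adds one reservation: "The exception will be with very small estimates of the relative risk of death (RR ≤ 1.3").

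**The concern.** One number cannot be both the rate in the whole cohort and the rate in the unexposed group if the exposed group has a higher risk. Table 2 shows the conflict directly. It holds the unexposed rate at 0.04826 while RR moves from 1.3 to 2.0. If 0.04826 is the cohort rate, the unexposed rate must differ in each column.

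The error runs in one direction. It inflates the baseline risk, hence the absolute difference, and so shrinks n. Tables 1 and 2 are the article's only stated basis for 80% power and for which relative risks it can detect. The Objectives also foresee nested studies with adequate sample power, so someone may reuse a figure such as 138 per group.

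**Working it through.** **Inputs.** Rates p, RRs and printed n come from Tables 1 and 2. Two-sided alpha of 0.05 is assumed, since sidedness is not stated; it reproduces the tables. The exposed share f in the source cohort is not given. I show f = 1/2 (the article's equal groups), 1/3 (a low tercile) and 0.10, all as assumptions.

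**Step 1: reproduce the tables.** The unpooled formula is n = (1.960 + 0.842)² × [p0(1−p0) + p1(1−p1)] / (p1−p0)², with p1 = RR × p0. For RR 1.91, p0 = 0.0495 and p1 = 0.09455, so n = 7.849 × (0.04705 + 0.08561) / 0.04505² = 514, as printed. The printed rates also give 816, 926 and 3,922 exactly, which confirms that the cohort rate was used as p0.

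The two high-RR columns do not match their printed rates. The formula gives 140 (printed 138) and 449 (printed 432). With p0 = 0.05 it gives exactly 138 and 432. At the printed rates these two columns start at 79.5% and 78.5% power, before any correction.

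**Step 2: correct p0.** The cohort rate is p = p0 × [1 + f(RR−1)], so p0 = p / [1 + f(RR−1)]. For RR 1.91 and f = 1/2, p0 = 0.0495 / 1.455 = 0.0340 and p1 = 0.0650. Then n = 7.849 × (0.03286 + 0.06076) / 0.03096² = 767.

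**Step 3: power at the printed n**, Φ(|p1−p0|/SE − 1.96):

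| Outcome, RR | Printed n | p0 at f = 1/3; 1/2 | Power at f = 0.10; 1/3; 1/2 | n needed at f = 1/3; 1/2 |
|---|---|---|---|---|
| Functional loss, 1.91 | 514 | 0.0380; 0.0340 | 76%; 68%; 63% | 683; 767 |
| Functional loss, 1.7 | 816 | 0.0399; 0.0365 | 77%; 71%; 67% | 1,021; 1,124 |
| Functional loss, 3.0 | 138 | 0.0296; 0.0246 | 71%; 56%; 48% | 246; 300 |
| Death, 1.66 | 926 | 0.0396; 0.0363 | 77%; 71%; 67% | 1,144; 1,254 |
| Death, 1.3 | 3,922 | 0.0439; 0.0420 | 79%; 76%; 74% | 4,338; 4,546 |
| Death, 2.0 | 432 | 0.0362; 0.0322 | 74%; 65%; 60% | 612; 693 |

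In the 138 and 432 columns, 0.5 and 1.5 points of the shortfall come from the rate mismatch in Step 1. The rest comes from the proxy.

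**Step 4: the planned cohort.** After 15% dropout, 2,750 × 0.85 ≈ 2,337 per group (4,675 in total). With f = 1/2 and equal groups, the lowest power outside the RR 1.3 column is about 97% (death, RR 1.66). With one third exposed in both the back-calculation and the group split, it is about 95.3% in the same column. At RR 1.3 with equal groups, power is 58% with the plan's rate and 52% at f = 1/2.

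**Step 5: smallest RR of death with 80% power after dropout**, solving the Step 3 expression for RR with SE² = p0(1−p0)/n0 + p1(1−p1)/n1:

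- plan's own rate, 2,337 per group: 1.40
- f = 1/2, 2,337 per group: about 1.44
- f = 1/3 in the back-calculation, and 4,675 split one third to two thirds: about 1.47

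At RR 1.4 with equal groups, power falls from 81% (plan's rate) to 73% (f = 1/2).

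**The case against.** The article calls the rate a proxy, so this is a disclosed approximation. The arithmetic that follows from it is right in four of six columns. Disclosure does not remove the bias, though, and the text does not say that it always favours the plan.

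A reader might infer that true power is 48% to 76%. The article does not support that as a fixed range. It joins the low end at f = 1/2 to the high end at f = 1/3, and the relevant f belongs to the outside cohort that supplied the rates. Shares from 5% to 67% give 42% to 79%. What stands is the direction: no share above zero restores 80%.

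The time unit of the rates is not stated. If they were annual (an assumption) and were converted to 3-year risks, power at the printed n would be about 90% or more in every column at f = 1/3 or 1/2, and the detection limits in Step 5 would change too. The tables, however, use the rates directly as proportions, and on that basis their n are wrong.

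The back-calculation is exact only for a two-level exposure and a crude RR. The text describes the unexposed both as medium or high IC and as high IC alone. That affects the size. It does not affect the direction, provided medium-IC risk is not below high-IC risk.

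A reader might also infer an underpowered study, or blame the proxy for the whole gap above RR 1.3. Neither holds. Five columns keep ample power at the planned size. With equal groups, the limit is already 1.40 before any correction.

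**Conclusion.** The point holds for the stated figures. Using the cohort rate as the unexposed rate is incompatible with RR above 1, and every n per group in Tables 1 and 2 is too small for its stated 80% power. The amount is conditional on f: power of 71% to 79% at f = 0.10, 56% to 76% at f = 1/3, and 48% to 74% at f = 1/2. All of these take the rates as proportions, as the tables do.

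Enrolment of 5,500 is not put in doubt at f = 1/3 or 1/2. The RR 1.3 column falls short, but the article already excepts it. The exception itself is drawn too low. On the tables' own basis, RRs of death between 1.3 and 1.40 lack 80% power after dropout even with the plan's rate, and the correction moves that limit to about 1.44 to 1.47. The consequence is misstated figures and a misstated detection limit. The study size does not fail.

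**What to change.** - In each column set p0 = cohort rate / [1 + f(RR−1)], with f the low-IC share in the cohort that supplied the rates. The share in LONGFUN's own planned contrast is not a substitute. If the source share is unknown, show a range of f.
- State the time unit of the rates and the period to which the proportions refer.
- Recompute all six n per group, including the two high-RR columns that do not match their printed rate.
- Replace the sentence on the exception with the smallest detectable RR of death for the group split that will be analysed, after dropout.
- Remove the statement that the cohort rate stands in for the unexposed rate.

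The cost is six recalculations, edits to two tables and two sentences, and slightly less favourable stated figures. No extra participants or procedures are needed.
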